**Remote follow up**

At the end of the study, with their permission, participants will be followed up remotely via office for national statistics tagging and routine general practice data collection.

**SAMPLE SIZE**

The primary outcome of the intervention trial will be reduced sedentary behaviour, measured by an accelerometer (time <100 counts/min as assessed by 1-week accelerometry) at 12 months. The minimum reduction in sedentary behaviour that would yield beneficial metabolic effects has not been determined. Cross-sectional data suggests that each 10% increase in sedentary time is associated with a 3.1cm increase in waist circumference, and that sedentary time is positively associated with clustered metabolic risk (Healy 2008). Using the same dataset, the mean sedentary time is 56.7 hours/week. Therefore, we suggest that a minimum clinically important difference would be 5.67 hours/week, reducing to 51.03 (SD 12.1). Sample size is estimated as 2N = (4(Za+Zb)2s2)/d2 (where d is the true between-arms difference, b is the type II error rate, and a is the type I error rate). Alpha is set at P = 0.05 (Za = 1.96) and power at 80% (b = 0.20, Zb =.842). This results in a required N of 72 in each arm. Incorporating a drop out rate of 25% gives a final N of 89 per arm.

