**PHASE 3: RANDOMISED CONTROLLED TRIAL**

In Phase 3, the STAND group structured education course will be delivered in a randomised controlled trial to 178 participants from across Leicestershire and the South East Midlands Diabetes research network.

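### The 25% drop-out allowance is miscalculated: 89 per arm gives about 77% power at that loss, not the stated 80%

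*Protocol*

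**What the plan says.** The Sample Size section of the protocol plans a two-arm comparison of mean accelerometer sedentary time at 12 months. It gives all the inputs:

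- Type I error: "Alpha is set at P = 0.05 (Za = 1.96"), which implies a two-sided test.
- Power: "power at 80% (b = 0.20, Zb =.842").
- Difference and SD: "a minimum clinically important difference would be 5.67 hours/week, reducing to 51.03 (SD 12.1").
- Formula: "Sample size is estimated as 2N = (4(Za+Zb)2s2)/d2", where the trailing 2s are squares.

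Its result is: "This results in a required N of 72 in each arm". The next sentence adds the allowance for loss: "Incorporating a drop out rate of 25% gives a final N of 89 per arm". The opening of Phase 3 carries the total forward, with the course "delivered in a randomised controlled trial to 178 participants", that is 2 × 89.

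No other section gives a different drop-out rate, another inflation rule, or a variance reduction that would lead to 89.

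**The concern.** A drop-out rate is a share of the people randomised. To finish with a required number, that number is divided by one minus the rate. Multiplying by one plus the rate always gives too few, and the gap widens as the rate rises. At 25% the multipliers are 1.25 and 1.333, so the error is large enough to matter.

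At stake is the power statement for the primary outcome. If loss reaches the level the protocol itself plans for, the trial falls short of the 72 per arm that its own calculation requires. A null result would then be read against 80% power that the calculation does not support, and the same justification would pass into the trial report.

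**Working it through.** **Inputs** (all from the Sample Size section): difference d = 5.67 hours/week, SD s = 12.1, Za = 1.96, Zb = 0.842, drop-out 25%, 89 per arm randomised.

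**1. Reproduce the evaluable number.**

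2N = 4(Za + Zb)² s² / d² = 4 × (2.802)² × (12.1)² / (5.67)² = 143.0

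This is 71.51 per arm, rounded up to 72, as stated.

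**2. Look for the source of 89.**

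| Calculation | Result per arm |
|---|---|
| 72 / 0.75 | 96 |
| 71.51 / 0.75 | 95.3 |
| 72 × 1.25 | 90 |
| 71.51 × 1.25 | 89.4 |

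Only multiplication by 1.25 lands near 89. The protocol does not show this step, so that explanation is inferred. A one-sided test does not explain the figure either: it would need 57 per arm, and 57/0.75 = 76.

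**3. What 89 per arm leaves.**

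89 × 0.75 = 66.75 per arm, against 72 required.

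**4. Power at that number, by the protocol's unadjusted comparison.**

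Standard error = 12.1 × √(2/66.75) = 2.094

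d / SE = 5.67 / 2.094 = 2.707

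Power = Φ(2.707 − 1.96) = 77.3%

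With whole participants this is 76.8% at 66 and 77.4% at 67 per arm. The noncentral t distribution gives 76.6% at 66.75.

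**5. Detectable difference at 80% power.**

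2.802 × 2.094 = 5.87 hours/week, which is 3.5% above the 5.67 that the protocol names as its minimum clinically important difference.

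**6. Loss that 89 per arm can absorb.**

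1 − 72/89 = 19.1%. From the unrounded 71.51 it is 19.7%.

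**7. Check of the corrected number.**

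96 × 0.75 = 72 per arm, where power is 80.3% by the normal approximation. The total would be 192, or 14 more than 178.

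**The case against.** **The shortfall is small and the inputs are soft.** The gap is about 3 points of power. The protocol says that the smallest beneficial reduction is not known, takes 10% of an external mean as its target, and calls the trial proof-of-concept. An SD of 11.7 instead of 12.1 would restore 80% at 66.75 per arm by the normal approximation. All this is fair, and it limits the size of the point. It does not make the drop-out step right, and the error touches neither the type I error nor the validity of the analysis.

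**The planned ANCOVA may recover the power.** The Data Analysis section specifies robust ANCOVA of change. If baseline is a covariate, the residual variance falls by the factor 1 − r², where r is the correlation between baseline and 12 months. By the normal approximation, 80% at 66.75 per arm needs r = √(1 − 66.75/71.51) = 0.26; a t-based calculation needs just under 0.30. At r = 0.5, power would be about 87%. So actual power may turn out above 80%. This stands as a qualification: the check shows that the stated calculation is wrong, not that the trial must be underpowered. But the sample-size calculation takes no credit for adjustment, no covariate is named, and no correlation is given. If change were analysed without adjusting for baseline, its variance would be 2(1 − r)s², and 80% power at this size would need r above 0.5.

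**Invalid recordings are a separate matter.** The Primary Outcome section requires four valid days of wear. The protocol does not say whether the 25% includes recordings that fail this rule. Counting them in the same allowance is an assumption, and nothing in the arithmetic depends on it.

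**Conclusion.** The concern holds. The 72 per arm is correct; the step from 72 to 89 is not. At the protocol's own 25% drop-out, 89 per arm leaves 66.75, and power is 77.3% (normal) or 76.6% (t) instead of 80%. The planned size supports 80% only up to about 19% loss.

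These figures rest on the protocol's difference, SD and unadjusted formula, and on reading the drop-out rate as a share of those randomised. The shortfall is modest, but it lies in the power claim for the primary outcome and should be corrected.

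**What to change.** Rewrite the last part of the Sample Size section. The simplest correction keeps 178 participants and states two things:

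- 89 per arm gives 80% power for up to 19% loss. Say whether loss here includes invalid accelerometer recordings as well as withdrawals; counting both is the safer definition.
- At 25% loss about 67 per arm remain, and power is about 77%.

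This costs one paragraph and a slightly less favourable power statement, with no extra participants.

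Two alternatives would also reconcile the figures, and the choice is the sponsor's:

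- Randomise 96 per arm (192 in total, 14 more) and change the total at the start of Phase 3 to match.
- Recalculate for a baseline-adjusted ANCOVA, naming baseline sedentary time as a covariate and stating and justifying the assumed correlation. About 0.26 to 0.30 is enough at 67 per arm, but the value has to come from outside this protocol, which gives none.

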**PROCESS EVALUATION**

Process evaluation will explore the implementation, delivery, context and reach of our STAND intervention. It will also allow us to develop and understanding of its impact on various sub-groups. The questions we wish to address are:

- What is the relation between trial outcome and variation in the extent and quality of the implementation of the intervention?
- What processes mediate the relation between intervention and outcomes?
- Do subgroups (e.g. age, ethnicity etc) differ in their responses to the intervention?

This process will involve quantitative and qualitative methods: questionnaire surveys, focus groups, interviews, researcher observations, and structured field notes during the delivery of the intervention. The identification of key mediating factors will facilitate later understanding and interpretation of the STAND intervention outcomes. Once 1 year follow up data have been collected we will have the opportunity to perform quantitative analysis of the impact of our intervention on various sub-groups (e.g. ethnicity) and mediators (e.g. course educators, location). By integrating our process and outcome data we will be able to develop a fuller understanding of our intervention components (Oakley 2006). This process will allow us to identify the relative merits of the intervention concept/theory and delivery/implementation (Rychetnik 2002).

**DATA ANALYSIS**

The study will be reported according to the CONSORT statement for randomised control trials. Data will be analysed on an intention-to-treat basis (ITT). Data will be analysed using STATA v10 and SPSS v16 software. Descriptive statistics (mean values and frequencies) will be calculated. Histograms will be used to identify any outliers and to test for normality. Robust ANCOVA modelling will be used to look at the difference between groups in change in continuous outcome measures and logistic regression will be used to analyse categorical variables. Results will be disseminated via peer-reviewed publications and presentations at national and international meetings.

#### CONCLUSION

#### This will be the first UK trial to address sedentary behaviour change in a population of young adults at risk of T2DM. The trial will inform behaviour change programmes for this at-risk group, and provide a major new direction of behaviour change alongside the more conventional approach of encouraging increases in moderate-to-vigorous physical activity. The results will provide a platform for the development of a range of future multidisciplinary interventions in this rapidly expanding high-risk population.

**
[figure not shown]
**

**TRIAL STEERING COMMITTEE AND TRIAL SPONSOR**

We will establish a Trial Steering Committee comprising lay members, the project Chief Investigator ([name]), Principal Investigator ([name]), the project manager, and upto two independent members with academic and clinical trial experience. Membership has yet to be determined. The trial sponsor will be UHL.

